## Abstract

**Background:**

Poor oral health, such as periodontal (gum) disease, has been found to be associated with an increased risk of adverse pregnancy outcomes including preterm birth, low birth weight, and neonatal and infant mortality, especially in low-and middle-income countries. However, there is little or no access to preventive dental care in most low-and middle-income countries. We propose to develop and test a “Mouth Rinse Intervention” among pregnant women to prevent the progression of periodontal disease during pregnancy and reduce adverse birth and neonatal outcomes in a rural county of China.

**Methods/Design:**

This is a randomized controlled clinical trial. A sample of 468 (234 in each arm of the study) women in early pregnancy with periodontal disease will be recruited for the study. Periodontal disease will be diagnosed through the methods of Periodontal Screening and Recording. All women diagnosed with periodontal disease will be randomly allocated into the intervention or control group. Women assigned in the intervention group will be provided with non-alcohol antimicrobial mouth rinse containing cetylpyridinium chloride throughout the pregnancy and oral health education. Women in the control group will receive a package of tooth brush and paste, plus oral hygiene education. Women will be followed-up to childbirth until the 42nd day postpartum. The main outcomes include mean birthweight (gram) and mean gestational age (week).

**Discussion:**

Compared with conventional mechanical ‘scaling and root planning’ periodontal treatment during pregnancy, our proposed mouth rinse intervention could be a simple, cost-effective, and sustainable solution to improve both mother’s oral health and neonate outcomes. If the mouth rinse is confirmed to be effective, it would demonstrate great potential for the application in other low- or middle-income countries to prevent adverse birth outcomes such as preterm birth and low birth weight and to reduce neonatal and infant mortality.

**Trial registration:**

This trial was registered with Chinese Clinical Trial Registry (ChiCTR): (#ChiCTR-TRC-13003768) on November 06, 2013.

## Background

Adverse birth outcomes, such as preterm birth and low birth weight, are the primary causes of infant morbidity and mortality in both developed and developing countries. Preterm birth complications lead to 35 % of world’s 3.1 million annual neonatal deaths [1]. A baby born with low birth weight (less than 2,500 g) had approximately 20 times risk to die than a baby with birth weight above 2,500 g [2]. Life course theory suggested negative birth outcomes including low birth weight and pre-term birth have lifelong effects, increasing the risk of chronic disease in adulthood [3]. As one of the developing countries, China is ranked as having the second highest (after India) number of neonatal and infant deaths in the world [4]. To tackle with and reduce the negative birth outcomes is an urgent task of achieving Millennium Development Goals and reducing susceptibility of adulthood chronic disease worldwide including China.

Systematic reviews have shown poor oral health, such as periodontal disease, is associated with an increased risk of adverse birth outcomes including preterm birth, low birth weight etc., especially in low- or middle-income countries [5–11]. But, several randomized controlled trials failed to show a significant reduction in preterm birth and low birth weight as a result of standard periodontal treatment in pregnant women with periodontitis [12–14].

As the standard therapy of periodontal disease, the scaling and root planning (SRP) during pregnancy itself possibly causes bacteremia thereby triggering a systemic inflammatory response, which may lead to adverse pregnancy and birth outcomes [15, 16]. Due to the safety reasons during pregnancy, the frequency of periodontal treatment are often restricted, with only one or two therapy courses, which might not sufficient to prevent the progression of periodontal disease [15, 17]. Therefore, it might be the SRP treatment itself that causes a failure of treating periodontal inflammations during pregnancy as well as preventing adverse birth outcomes.

In many poor and low-income areas, there is the universal shortage of qualified dental human resources [18–20]. The conventional SRP periodontal treatment is often unavailable for most of grass-roots. A simple, affordable and practical oral health care to prevent the progression of periodontal disease is needed. A recent clinical trial conducted in the U.S. has demonstrated that the use of non-alcohol antimicrobial mouth rinse containing cetylpyridinium chloride (CPC) results in a significantly reduced incidence of preterm birth and low birth weight in pregnant women with high risk, and that its use is safe to pregnant women [21]. Antimicrobial mouth rinse containing CPC is an attractive approach for gestational oral health care as its inexpensive cost and the capability of reducing bacterial plaque, gingival inflammation and periodontal disease without additional periodontal intervention [21]. In addition, it is easy to be implemented without the requirement of the operation by dental professionals [21]. However, this mouth rinse intervention has not been tested to prevent adverse birth outcomes in low resource settings, like in rural regions of China. Therefore, we proposed to conduct a randomized controlled trial (RCT) to examine whether a “Mouth Rinse Intervention (MRI)” during pregnancy would reduce adverse birth outcomes in a rural area of China.

### Objectives and hypotheses

The objective of this study is to develop and test aMRI among pregnant women to prevent the progression of periodontal disease during pregnancy and reduce adverse birth and neonatal outcomes in a rural county of Jiangxi Province, China.

### We hypothesize that the MRI will

increase birth weight and prolong gestational duration;reduce progression of periodontal disease during pregnancy;improve neonatal health; andbe acceptable and applicable in resource limited rural areas.

The primary outcomes are mean birth weight (grams) and mean gestational age (weeks). The secondary outcomes are periodontal index determined by the total code of periodontal examination in each sextant of the mouth, compliance of the use of antimicrobial mouth rinse, and rate of admission to Neonatal Intensive Unit (NICU).

## Methods/design

### Overall study design

This is a randomized controlled trial. Pregnant women less than 20 gestational weeks are eligible to participate in a quick periodontal disease screening. Women who meet the criteria and are diagnosed with periodontal disease will then be randomized into two groups: an intervention or MRI group, versus a control group. All participants will be followed throughout their pregnancy and their babies’ 42 postnatal days (see Fig. 1).

**Fig. 1 Fig1:**
[figure not shown]
Research flow chart

Ethical approval to conduct this trial has been granted by the Institutional Review Board of School of Public Health, Fudan University, Shanghai, China (IRB# 2013-09-0462); and also by the Institutional Review Board of Tulane University, New Orleans, Louisiana, USA (IRB# 13–469160). The research is registered with Chinese Clinical Trial Registry (#ChiCTR-TRC-13003768).

### Participants and recruitment

This RCT will be conducted at the Maternal and Child Health Care Hospital, in Leping, Jiangxi Province, China. Leping County locates in the southeast China, with a population of 900,000. The hospital is the only maternal and child health care hospital in the county, with a total of 4,000 deliveries annually (covering more than 40 % of deliveries in the county). There are both prenatal health care and dental clinic in the hospital.

Recruitment will be conducted among pregnant women attending prenatal health care at the hospital. All women attending prenatal health clinics, with less than 20 gestational weeks, will be approached and invited to participate in the study by research nurses. If pregnant women agree to participate in the study, they will be assessed for the eligibility. Eligible women will be provided with a free dental examination for screening periodontal disease. Women who meet the criteria of periodontal disease will be randomized into the intervention and control groups. Written informed consent will be obtained from each participant before the randomized group allocation is revealed.

### Inclusion criteria

Pregnant women with gestational age less than 20 weeksAt least 18 years old;Planning to deliver at the recruiting hospital

Additional inclusion criteria for randomization:Diagnosed as having periodontal disease after a dental examinationAt least 20 teethWithout moderate or severe dental cariesWithout systemic disease, including severe cardiovascular disease, diabetes, hyperthyroidism, and/or other systemic diseasesWithout reproductive disease such as infertility, and sexually transmitted diseases including syphilis, gonorrhoeae, trichomonas, mycotic vaginitisWithout immunodeficiency diseasesWilling to be compliant to follow up until baby’s 42 postnatal days

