### Sample size

#### Sample size calculation for primary outcomes

We calculated that a consecutive sample of 422 (211 in each arm of the study) pregnant women with periodontal disease will be required for the study, at 0.05 significance level with 80 % power. The sample size calculation is based on detecting changes in primary outcome of birthweight. To detect a difference in mean birthweight of 100 g between the groups, a sample size of 211 for each group is needed. This was based on an estimation of SD as 380 g in the intervention group and SD as 350 g in the control group. Given the estimated 10 % of loss to following up during pregnancy, a total of 468 women in early pregnancy with periodontal disease will be needed. With the estimation of 75 % prevalence of periodontal disease (from another study in urban area) [17], 624 women in early pregnancy will be recruited for periodontal disease screening. A total of 234 pregnant women with periodontal disease will be needed, at 0.05 significance level with 80 % power, if the sample size calculation is based on changes in mean gestational week to detect a difference of 0.5 week between two groups, with SD 1.5 week and 1.2 week in each group respectively. We use the larger sample size as the final amount for recruiting.

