### Data analysis plan

Descriptive statistics will be performed to examine for all outcomes and covariates. For continuous variables, such as periodontal code, birth weight (gram), gestational age (week) will be compared using t-tests, or non-parametric equivalents for non-normally distributed variables. For categorical variables such as the rate of periodontal disease and rate of admission to NICU, chi-squared tests will be used. All outcomes will be compared between the intervention and control groups. All analyses will be conducted with “intention to treat” analysis [25].

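### Eligibility does not require a singleton pregnancy, although both primary outcomes are means on which twins are expected to fall low; the cost is some birth-weight power, not bias

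*Protocol article*

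**What the plan says.** Under *Inclusion criteria*, the conditions for entering screening are "Pregnant women with gestational age less than 20 weeksAt least 18 years old;Planning to deliver at the recruiting hospital" (the list items run together in the extracted text). The additional conditions for randomization cover periodontal disease, number of teeth, caries, systemic, reproductive and immune disease, and willingness to be followed up. *Exclusion criteria* adds contraindications to probing, recent periodontal treatment and lack of consent. Neither list mentions plurality. *Participants and recruitment* has the nurses approach all women under 20 weeks who attend the prenatal clinics, and no other section shown deals with multiples.

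The outcomes are fixed in the list of hypotheses: "The primary outcomes are mean birth weight (grams) and mean gestational age (weeks").

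On size, *Sample size calculation for primary outcomes* says "To detect a difference in mean birthweight of 100 g between the groups, a sample size of 211 for each group is needed", and adds "This was based on an estimation of SD as 380 g in the intervention group and SD as 350 g in the control group". No source is given for these SDs. For gestational age the target is "to detect a difference of 0.5 week between two groups, with SD 1.5 week and 1.2 week in each group respectively". The counts are of women: "Given the estimated 10 % of loss to following up during pregnancy, a total of 468 women in early pregnancy with periodontal disease will be needed".

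Under *Data analysis plan*, "birth weight (gram), gestational age (week) will be compared using t-tests, or non-parametric equivalents for non-normally distributed variables", and all analyses are to follow intention to treat.

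**The concern.** The lists are itemised and already remove several maternal conditions, infertility among them, so a singleton condition would fit their design. Excluding infertility may remove some twins from assisted conception, but not spontaneous ones.

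A twin pregnancy is expected to give low values on both primary outcomes whichever arm the woman is in. A small number of such women widens the distribution of birth weight. The sizing for that outcome has no slack: 211 per arm gives almost exactly the stated 80 % power, and 468 women less 10 % leaves 468 × 0.9 = 421. Variance beyond the planning SDs therefore takes power below 80 %.

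**Working it through.** **Inputs from the protocol.** Birth weight: difference 100 g, SDs 380 and 350 g, 211 per arm. Gestational age: difference 0.5 week, SDs 1.5 and 1.2 weeks, 234 women in total. Significance level 0.05 (two-sided assumed), power 80 %.

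**Inputs assumed, not in the documents.** Share of women carrying twins p = 1-3 %. Birth-weight deficit d = 700-1000 g. Gestational deficit 2-4 weeks. The stated SDs describe singletons. Each mother contributes one value, with the same spread around the twin mean as around the singleton mean.

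**Step 1: the plan's own figure.** Mean variance = (380² + 350²)/2 = (144,400 + 122,500)/2 = 133,450, so SD = 365.3 g. Then n per arm = (1.960 + 0.842)² × 2 × 133,450 / 100² = 209.5, that is 210. The t-based solution is 210.5, that is 211. The stated 211 is reproduced. Normal-approximation power at 211 is Φ(100/(365.3 × √(2/211)) − 1.96) = Φ(2.812 − 1.960) = 80.3 %.

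**Step 2: birth weight with twins admitted.** The added variance is p(1 − p)d².

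| p | d (g) | Added variance | Rise | SD (g) | Needed per arm | Power at 211 |
|---|---|---|---|---|---|---|
| 0 | – | 0 | – | 365.3 | 210-211 | 80.3 % |
| 1 % | 700 | 0.0099 × 490,000 = 4,851 | 3.6 % | 371.9 | 218 | 78.9 % |
| 2 % | 900 | 0.0196 × 810,000 = 15,876 | 11.9 % | 386.4 | 235 | 75.7 % |
| 3 % | 1000 | 0.0291 × 1,000,000 = 29,100 | 21.8 % | 403.2 | 256 | 72.2 % |

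**Step 3: gestational age.** Mean variance = (1.5² + 1.2²)/2 = 1.845, SD 1.358 weeks. The t-based solution is 117 per arm, which reproduces the stated total of 234. At 211 per arm, power for 0.5 week is 96.6 % without twins. With 1 % twins and a 2-week deficit it is about 96 %, with 2 % and 3 weeks 95.1 %, and with 3 % and 4 weeks 92.2 %.

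**Step 4: chance imbalance.** Among 422 women, 1-3 % means about 4 to 13 twin pregnancies (422 × 0.01 = 4.2; 422 × 0.03 = 12.7). With one value per mother, one extra twin pregnancy lowers its arm's mean by 900/211 = 4.3 g (3.3-4.7 g for 700-1000 g). An imbalance of three gives 3 × 4.3 = about 13 g (10-14 g). The probability of an imbalance of three or more is 21 % at p = 1 %, 38 % at 2 % and 47 % at 3 %.

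**Step 5: is the imbalance a further harm?** At p = 2 % and d = 900 g, the twin component of the standard error of the difference is √(2 × 15,876/211) = 12.3 g. The remaining component is √(2 × 133,450/211) = 35.6 g. Together they give √(12.3² + 35.6²) = 37.6 g, which is the standard error implied by the SD of 386.4 g in step 2. The imbalance is therefore already counted in the power loss.

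**The case against.** The strongest reply is that nothing in the lists is false or contradictory, that an article condenses a fuller protocol, that the flow chart is not visible, and that the power loss rests wholly on outside assumptions. Part of this stands. The planning SDs have no stated source; if they come from all deliveries, twins are already allowed for, in part or in full. At the low end the loss is little more than one percentage point (80.3 % to 78.9 %). What does not stand is that eligibility can be left to an analysis plan: the criteria are printed item by item, and followed as written they admit multiples.

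A reader might infer four stronger things, and the documents support none of them.

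- *The unit of analysis is broken.* The sizing counts women, and no section proposes treating each infant as an independent subject. The rule for siblings may stand in an analysis plan not shown.
- *Each twin pair moves an arm mean by 8.5 g.* That figure counts both infants (2 × 900/212). Per mother it is about half.
- *Imbalance biases the result.* Allocation is random, so it is sampling error, already counted in step 5.
- *Both primary outcomes lose adequate power.* Gestational age does not.

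**Conclusion.** The point holds as a cheap improvement to eligibility. That multiples are admitted follows from the text alone. The size is conditional: with 1-3 % twin pregnancies, a 700-1000 g deficit, singleton planning SDs and one value per mother, birth-weight power falls to about 72-79 %, and 218-256 per arm would be needed to restore 80 %. If the SDs already reflect a population with twins, the loss shrinks or vanishes. Gestational-age power remains above 90 % throughout the assumed range. The trial's validity is not at stake; the precision of its birth-weight comparison is.

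**What to change.** Add singleton pregnancy to the additional criteria for randomization under *Inclusion criteria*.

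For a multiple pregnancy recognised only after randomization, choose one of two rules in advance. Either keep the intention-to-treat set of the *Data analysis plan*, with one predefined value per mother, and report the singleton-only comparison alongside. Or amend that section beforehand so that the singleton comparison is primary. The second is defensible because plurality is a baseline characteristic that allocation cannot affect, but without the amendment it conflicts with the stated intention-to-treat rule.

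It would also help to state whether the planning SDs come from singletons or from all deliveries.

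The cost is one line, an assumed 1-3 % of otherwise eligible women, and results that no longer extend to multiples. To randomise 468 singletons, about 468/0.99 = 473 to 468/0.97 = 483 otherwise eligible women would be needed, 5 to 15 more.

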### Exclusion criteria

Less than 18 years oldFewer than 20 teethContraindication to probing in a dental examination, such as heart disordersUnwilling or unable to sign the informed consent formReceiving periodontal treatment within the past six monthsWith a disease mentioned in the inclusion criteria.

### Enrollment and randomization procedures

Random allocation to either the intervention or control group is decided by a computer generated random number. The group allocation will not be concealed until pregnant women have completed the dental examination, identified with periodontal disease and signed the informed consent. Research nurse will unseal the opaque envelopes and inform the women about the group allocation. A research group member who has no direct contact with participants will be responsible for generating the random numbers and preparing the envelopes.

### Intervention group

Women in the intervention group will be provided with free mouthwash (alcohol-free antimicrobial mouth rinse containing 0.7 % CPC) throughout the whole pregnancy and oral health education. All the women will be provided with detailed instructions regarding how to use the mouth rinse: twice daily for 30 seconds with the supplied rinse (after regular tooth brushing), and will be asked to keep a diary. This rinse mouthwash has been used in a study among pregnant women and has proved to be safe [21]. Pregnant women will be provided with the rinse mouthwash from the prenatal health care clinic at each month when they have the prenatal check-up. At the third trimester between 32 and 35 gestational weeks women in the intervention group will be requested to have dental re-examination. If women have preterm delivery prior to 32 gestational weeks, the measurement within two days of childbirth will be used to reflect the periodontal status during late pregnancy.

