## Discussion

We proposed to conduct a RCT to assess a MRI among pregnant women to prevent the progression of periodontal disease during pregnancy and to improve birth and neonatal outcomes. As perinatal oral health care usually not available in rural China, our proposed intervention will be the first study aiming to explore a convenient, affordable, acceptable oral health care package in rural China. If the intervention is effective, it will be more acceptable than the conventional and standard periodontal therapy by women, and have potential generalizability to other similar poor areas, where childbearing aged or pregnant women have very limited access to oral health care.

The conventional periodontal therapy mainly includes “SRP,” which involves mechanically cleaning the teeth above and below the gum line by removing the etiologic agents that cause inflammation. However, due to the high cost, the demand for expensive dental equipment, and the need for professional dentists in order to perform periodontal therapy, as well as concerns regarding the safety of the therapy, this conventional periodontal therapy may not be feasible to apply in low resource settings. In addition, we use a rapid PSR for the screening periodontal disease. Compared to the conventional full-mouth dental examination, the PSR takes only a few minutes to conduct for each patient, does not require the use of expensive dental equipment, and can be performed by non-oral health professionals after receiving appropriate training, which is particularly applicable to economically poor regions. The proposed non-alcohol, 0.07 % CPC antimicrobial mouth rinse is commercially available and cheap; and it has been previously shown to be safe and to decrease the severity of periodontal disease and the rate of preterm birth and low birth weight [21].

Due to limited the research funding and study period, the sample size of this study is relatively small, not allowing for the observation of the birth outcomes as proportions e.g. the rate of low birth weight and the rate of preterm birth. If there is evidence of effectiveness after this initial study, we will seek further funding to expand the trial, with birth outcomes in proportions as primary outcomes.

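### The strength of the trial mouth rinse is given as 0.7 % CPC in the Intervention group section and 0.07 % CPC in the Discussion, a tenfold contradiction that the article does not resolve

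*Protocol article*

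**What the plan says.** The Intervention group section of the protocol article defines what women in the active arm receive: free mouthwash, described as an "alcohol-free antimicrobial mouth rinse containing 0.7 % CPC", used for 30 seconds twice daily after brushing and supplied monthly throughout pregnancy. The same section supports its safety with an earlier study: "This rinse mouthwash has been used in a study among pregnant women and has proved to be safe [21".

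The Discussion returns to the product with a different strength: "The proposed non-alcohol, 0.07 % CPC antimicrobial mouth rinse is commercially available and cheap". The sentence continues that "it has been previously shown to be safe and to decrease the severity of periodontal disease", and adds lower rates of preterm birth and low birth weight, again citing reference 21.

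The Abstract (Methods/Design) names the agent without a strength: "non-alcohol antimicrobial mouth rinse containing cetylpyridinium chloride throughout the pregnancy and oral health education". The Background, summarising reference 21, also gives none: it reports that "the use of non-alcohol antimicrobial mouth rinse containing cetylpyridinium chloride (CPC) results in a significantly reduced incidence of preterm birth".

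**The concern.** A single product cannot have two strengths. The trial has one rinse, since controls receive a toothbrush, paste and education instead, so both figures must refer to the same bottle.

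Strength is a defining property of the intervention. The women enter before 20 weeks of gestation and are to use the rinse until birth. The article does not generate its own safety or efficacy case for the rinse: it borrows both from reference 21. That evidence carries over only if the trial rinse has the strength studied there. If product were bought to the wrong figure, the safety statement in the Intervention group section would no longer be supported.

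Replication is also at stake. The article aims at wider use in other low-resource settings. A team repeating the trial would naturally take the strength from the Methods, and could specify a rinse tenfold away from the one named in the Discussion.

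**Working it through.** No sample-size or power formula is involved. The check compares every place where the article names CPC or describes the rinse.

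| Section of the protocol article | Strength stated | Link to reference 21 |
|---|---|---|
| Abstract, Methods/Design | none | none |
| Background | none | summarises its results |
| Intervention group | 0.7 % | cited for safety |
| Control group | none (rinse not given) | none |
| Records of use of mouth rinse | none | none |
| Discussion | 0.07 % | cited for safety and benefit |
| Abbreviations | none (expands CPC only) | none |

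**Step 1: do the two figures describe one product?** Yes. The Intervention group section describes what the active arm is given, and the Discussion speaks of the proposed rinse. Both attach the same reference for its safety.

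**Step 2: how large is the gap?** 0.7 / 0.07 = 10. The digits match and only the decimal place differs, which points to a slip and rules out rounding.

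**Step 3: what does that mean as a concentration?** The article does not say how the percentage is defined. Assuming weight per volume:

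- 0.7 % = 0.7 g per 100 mL = 7 mg/mL
- 0.07 % = 0.07 g per 100 mL = 0.7 mg/mL

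No volume per rinse is given, so no dose per use can be derived. The ratio of 10 holds at any volume, and also if both percentages are weight per weight.

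**Step 4: can the article settle which is right?** No. CPC is named in five places (Abstract, Background, Intervention group, Discussion, Abbreviations), and only two of them give a strength. No brand is named from which the strength could be looked up. The Discussion calls the rinse commercially available, and both sections point to reference 21, but neither statement fixes a number within the document.

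**Step 5: does the error reach the statistics?** No. The sample size rests on a 100 g difference in mean birth weight with SDs of 380 g and 350 g. The check on gestational age uses 0.5 week with SDs of 1.5 and 1.2 weeks. Rinse strength enters neither calculation, nor the analysis plan.

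**The case against.** The strongest reply accepts the contradiction and disputes its weight. This looks like a one-character misprint. The rinse is described as a commercial product and as the one used in reference 21, and nothing suggests that the trial team mixes it to a strength. The maker would then fix the concentration, and a wrong digit in an article need not reach the bottle. Two ethics boards approved the trial and an independent safety board is in place, so the printed text is not the only safeguard. Nothing in the design or analysis depends on the figure.

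Most of this stands as a limit on what can be claimed. No wrong exposure is shown, and a harmless misprint is the likeliest explanation. It does not remove the need for correction. The 0.7 % figure sits in the section that specifies the intervention, where it is part of the specification and not a background remark. The assurance that the rinse is the one in reference 21 cannot be checked against a strength while the article states two. The ethics approvals and the safety board do not tell a reader which number is right.

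**Conclusion.** The concern holds. The article states the strength of its only test product twice, in current text, and the figures differ by a factor of 10. At least one is wrong, and the article gives no basis for choosing between them. This conclusion needs no assumption beyond reading both sentences as describing the trial's own rinse, which their wording and shared reference support. Only the mg/mL values depend on the weight-per-volume assumption.

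It must be fixed because it concerns what pregnant women are given and whether the cited safety evidence applies. It is not evidence that anyone received the wrong strength, and it has no bearing on the validity of the statistical design.

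**What to change.** Before dispensing, check the strength on the product label and in reference 21, and confirm that the two agree. Then state that single concentration in both the Intervention group section and the Discussion. Naming the product and saying whether the percentage is weight per volume would prevent the ambiguity from recurring.

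If the label matches one of the printed figures, one number in one section changes. If it matches neither, both change. If the label and reference 21 disagree, the statements that this rinse has already been shown to be safe and effective would need rewording, and the safety board should be told.

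The cost is a label and reference check and a short text correction. Nothing in the sample size, randomisation or analysis needs to be redone.
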